This protocol describes the population surveys that constitute a core component of the CAIR project. The surveys will be conducted twice during the project period—before and after the co-creation process—to capture changes over time in key indicators at the municipal district level. The surveys will generate quantitative evidence on the potential effects of moving from a predominantly biomedical model to one that embeds community participation and collective action in efforts to improve health.

Therefore, the aim of this study is to analyse changes in health-related quality of life, critical health literacy, social and community capital, and knowledge, attitudes, and practices regarding personal antibiotic use—and their implications for health equity—through population surveys conducted before and after the co-creation process in the Municipal District 2 of Elche, Spain.

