### Study setting

2.2

We will conduct a representative population-based survey among adult residents (≥18 years) in Municipal District 2 of Elche, Spain (Figure 1). This district includes the neighborhood of Carrús where resides 17.2% of the population of the city of Elche, with 36,065 residents in 2024. It is a diverse area, with 25.6% foreign-born residents, mainly from Morocco (6.2%), Colombia (5.3%), and Romania (3.1%) (10), as well as approximately 250 Roma families (11). The area shows levels of social vulnerability, with a high concentration of migrants and lower income levels. The Roma community faces structural discrimination and barriers to accessing education and employment, which negatively affect their wellbeing and opportunities (11).

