### Sample size estimation and selection criteria

2.4

The sample size has been calculated assuming that the prevalence of the variables of interest (e.g. proportion of individuals with poor health-related quality of life, proportion of individuals with limited critical health literacy etc.) does not exceed 30%, with an absolute precision of ± 5% and a confidence level of 95%. A design effect of 1.5 has been applied, following the recommendations of the World Health Organization's (WHO) STEPS guidelines (13) for complex designs. In addition, a rejection rate of up to 20% has been considered, implying the need to recruit at least 590 participants. The proposed inclusion of 600 participants also ensures the estimation of indicators for specific subgroups (such as by sex) with an absolute precision of close to ± 5%.

A before-and-after analysis will be conducted with 600 independent participants at each time point, selected using comparable samples and applying the same inclusion criteria and sampling design. This sample size is sufficient to detect significant differences in both our main outcome (i.e., health-related quality of life) and secondary variables. In the case of health-related quality of life, it allows us to identify absolute changes of around 10%, with a confidence level of 95% and a statistical power close to 80%. The exact power will depend on the initial prevalence of the indicator and the magnitude of the observed effect. Although the analysis of social inequalities may have lower power due to stratification by subgroups, we estimate that the sample size will be sufficient to identify relevant trends and significant differences in social inequalities in the studied sample.

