### Data analysis

2.8

As main outcome, the mean and the standard deviation of the health-related quality of life will be calculated and stratified by sex, age group and other sociodemographic variables, thus allowing for an equity analysis. In addition, we will perform multivariate models to analyse the association of sociodemographic characteristics on health-related quality of life and secondary variables (critical health literacy, social capital, community capital, and knowledge, attitudes and practices on personal antibiotic use). These results will be also crucial to enrich the discussions in the co-creation process, facilitating an equitable and contextualized approach to the identified health issues. A before-and-after analysis will also be carried out using the population-based survey data to assess changes across time points (pre- and post-intervention) in the population in both main and secondary variables, providing evidence on the evolution of health-related quality of life and other relevant social determinants of health. Specifically, firstly, the normal distribution of physical and mental HRQoL will be tested by conducting Shapiro-Wilk tests and plotting histograms. In case of observing a non-normal distribution, these variables will be dichotomised using the median value of the whole sample (pre- and post-intervention). Therefore, given the distribution of health-related quality of life, multivariate linear regression models or Poisson regression models with robust standard errors will be used to estimate absolute and relative changes across time points. Additional models will be run, including interaction terms of time with sex, age group and other sociodemographic variables to assess the changes in social inequalities in HRQoL. Contextual variables will be included, such as economic development, unemployment rate and poverty rate at the regional level of the province of Alicante before and after the intervention, retrieved from the National Institute of Statistics (INE) and the statistics portal of the Valencian Community in Spain. Statistical analysis will be adjusted for sex, age group and other sociodemographic variables such as education, ethnicity, migration status, household income, employment status and marital status, among others. Multiple imputation will be used for missing data on HRQoL and secondary variables. For the remaining covariates, an additional category of missing values will be created to include these individuals in the statistical analyses.

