It is essential to adopt more holistic approaches that combine biomedical interventions with non-pharmacological strategies, promoting active community participation and addressing both the underlying causes of health problems and the social inequalities that shape them. The implications of the study are not only on analyzing the potential effects of co-created actions on health and health equity, but also on generating evidence to decision-makers that community-centered, intersectoral approaches may strengthen health system performance and contribute meaningfully to better outcomes at a population level.

The use of repeated population surveys is a strength of this study, as it enables the assessment of change over time through before-and-after comparisons of carefully selected indicators that are directly relevant to co-creation processes. However, an important limitation of the overall design is the absence of a control area where no co-creation activities are implemented. As this is not a controlled trial, we cannot fully disentangle the effects of the interventions from broader contextual changes occurring over the same period. Therefore, the results obtained from the before-and-after analysis should be interpreted with caution. Various external and contextual factors, such as other policy measures implemented for the general population, economic and social changes, or changes in access to healthcare, may also influence the evolution of our primary health outcome despite controlling for macro-level variables. Moreover, different, independent participants will be recruited at baseline and after the intervention, which also limits the effects attributable to the co-creation intervention process. In this regard, our analysis should be interpreted as time-trend changes in the Municipal District 2 of Elche where targeted cocreation is taking place rather than changes among individuals taking part in the cocreation intervention.

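### Province-level context variables are perfectly collinear with the pre/post term, so the planned macro-level adjustment of the before-after change cannot be achieved

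*Protocol article*

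**What the plan says.** The Data analysis section (2.8) of the protocol article plans multivariable linear or Poisson models for the main outcome, health-related quality of life. Of the models it says "Poisson regression models with robust standard errors will be used to estimate absolute and relative changes across time points", so the pre/post coefficient carries the before-after result. Further models add interactions of time with sex, age group and other characteristics.

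The section then states: "Contextual variables will be included, such as economic development, unemployment rate and poverty rate at the regional level of the province of Alicante". The rest of that sentence fixes place and timing: the figures are taken "at the regional level of the province of Alicante before and after the intervention, retrieved from the National Institute of Statistics (INE" and a regional statistics portal. No smaller geographic unit and no finer time scale is given.

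The same section adjusts for individual characteristics, among them household income and employment status.

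In the Discussion, the limitations paragraph warns that outside factors such as other policies, economic and social change and access to care "may also influence the evolution of our primary health outcome despite controlling for macro-level variables". That wording presents the macro-level adjustment as something the analysis will carry out.

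**The concern.** A covariate can adjust a comparison only if it varies within the groups being compared, or if there are more groups than parameters. Here there are two groups, baseline and post-intervention, and everyone in a group shares the same province. A provincial indicator with one value per wave therefore relabels the wave and brings no further information.

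Two things are at stake. First, the model as described cannot be fitted with both sets of terms, so something will have to be dropped after the data are in. Second, readers are told that bias from economic change is what remains after macro-level control, although no such control is possible in this design.

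**Working it through.** The plan gives no figure on this point to reproduce. The check is of what the stated model can identify.

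**Inputs from the protocol article**
- Area (Study setting): "We will conduct a representative population-based survey among adult residents (≥18 years) in Municipal District 2 of Elche, Spain". One district, in one province.
- Comparison (Discussion): "the absence of a control area where no co-creation activities are implemented".
- Waves (Introduction): "The surveys will be conducted twice during the project period".
- Participants (Sample size estimation): "A before-and-after analysis will be conducted with 600 independent participants at each time point".
- Context variables (Data analysis): economic development, unemployment and poverty, for the province.

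**Step 1. Algebra.** Let T = 0 at baseline and 1 afterwards, and let a provincial variable Z take the values z0 and z1. For every respondent, Z = z0 + (z1 − z0)T. The linear predictor is then

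b0 + b1·T + c·Z = (b0 + c·z0) + [b1 + c(z1 − z0)]·T.

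Only the bracketed sum is identified; b1 and c separately are not. With three provincial variables, four unknowns (b1 and three c's) share that one identified quantity, so the three cannot be separated from each other either. This holds for the linear and the Poisson model alike, because both use the same linear predictor. If z0 = z1, the variable is constant and aliased with the intercept.

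**Step 2. Rank.** Design matrix for 600 + 600 participants: intercept, time, sex and three indicators for four age groups. The provincial values are assumed placeholders (unemployment 13 then 11, economic development 22 then 24.5, poverty 27 then 25). Any differing pairs give the same ranks.

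| Model | Columns | Rank | Time coefficient identified |
|---|---|---|---|
| Individual covariates and time | 6 | 6 | yes |
| + unemployment | 7 | 6 | no |
| + all three provincial variables | 9 | 6 | no |
| + all three and time × sex | 10 | 7 | no (time × sex: yes) |

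A larger sample does not change these ranks.

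**Step 3. What dropping a column does.** If the provincial terms are dropped, the time coefficient is the change adjusted for individual covariates only. If time is dropped and unemployment kept, the unemployment coefficient is that same change divided by (z1 − z0), here 11 − 13 = −2. The two fits have the same fitted values and the same one-degree-of-freedom test of change between waves. Only the label and scale differ.

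**Step 4. Sensitivity to finer timing (all values assumed).** Suppose unemployment were quarterly, with two quarters equally represented in each wave, a 2-point gap between waves and a spread w within a wave. The between-wave variance of Z is (2/2)² = 1 and the within-wave variance is (w/2)². So R² with time is 1/(1 + w²/4), and the variance inflation factor (VIF) is 1 + 4/w².
- w = 0.2: VIF 101, standard error about ×10
- w = 0.5: VIF 17, standard error about ×4.1
- w = 1.0: VIF 5 (R² = 0.8), standard error about ×2.2

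Adding one variable with a single value per wave, such as an annual poverty rate, makes the model singular again: intercept, time, quarterly unemployment and annual poverty are 4 columns with rank 3.

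**The case against.** **The before-after result survives.** A reader might infer from the rank deficiency that the change between surveys cannot be estimated at all, or that it depends on which column the software drops. Neither follows. Step 3 shows that the fit and the test are the same whichever column goes, and the change adjusted for individual covariates is fully estimable. The equity analysis through time-by-sociodemographic interactions is also intact. This part of the objection stands and limits the point to the macro-level adjustment.

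**The limitation is already disclosed.** The Discussion acknowledges that there is no control area, asks for caution, and tells readers to interpret the results as time trends in the district. It would be unfair to say that the paper invites a causal reading without warning. The caveat still presumes, in one subordinate clause, that macro-level control has been applied, and that clause is wrong.

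**One value per wave is an inference.** The article gives no reporting frequency and no length of fieldwork. A reader might suppose that quarterly values would still be almost completely collinear with wave. The documents do not support that as a general statement, since the assumed values in Step 4 give a VIF from about 5 to 101. But the stated timing is pre and post only, and any variable available once per wave restores the singularity.

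**The sentence may concern only the interaction models.** It follows the sentence describing them. The time main effect is unidentified there too, and the Discussion links the macro-level control to the primary outcome.

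**An analysis plan could settle it.** It could add detail, but it could not make this combination of terms estimable with one province, two waves and one value per wave.

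**Conclusion.** The point holds in a limited form. As written, the provincial variables add between one and three columns and no rank, so they provide no adjustment beyond the time term. A context-adjusted before-after change is not identified, and the Discussion's statement of macro-level control is not met. This rests on each indicator having one value per wave, which is what the Data analysis section describes, and it does not depend on the values themselves or on the sample size.

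What remains sound is the change adjusted for individual covariates, its test, and the interactions of time with sociodemographic variables. It would also go too far to say that nothing in the plan addresses economic change: household income and employment status vary within each wave and may capture part of it. What cannot be separated from time is the province-wide shift beyond that part.

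**What to change.** - In Data analysis, remove the province-level variables from the before-after regression models and report their values descriptively as the context of each wave.
- In the Discussion, delete the closing words of "may also influence the evolution of our primary health outcome despite controlling for macro-level variables" that claim macro-level control.
- Add one sentence in their place: beyond what individual covariates such as household income and employment status capture, province-wide secular change cannot be separated from the time effect with two waves and no comparison area.
- Do not substitute census-section indicators for the provincial ones. They address differences between sections, not a shift across the whole province between waves.

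The cost is a wording change in one analysis paragraph and one limitation sentence, with no new data or participants. The second survey is planned for 2029, so the change can be made before any post-intervention data exist.

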### Study design

2.1

The CAIR study applies a community-based participatory approach to engage citizens in co-creating initiatives to improve health and wellbeing. To evaluate their effect in the Municipal District, we will conduct representative population-based surveys before and after the three-year co-creation period (2026–2028). These surveys will measure health-related quality of life, critical health literacy, social and community capital, and knowledge, attitudes, and practices related to personal antibiotic use, alongside key sociodemographic characteristics to enable an equity-focused analysis. Baseline results will inform the co-creation process by identifying community needs, health status and health inequities, ensuring that initiatives are designed to address them effectively and fairly. Changes over time will be assessed by comparing indicators between surveys before and after the co-created intervention process, also estimating absolute and relative differences across population groups.

The broader CAIR project is registered on ClinicalTrials.gov (Identifier: NCT07237971). CAIR began on 1 October 2024 and will run for 5 years. Recruitment for the baseline survey started on 22 October 2025 and the post-intervention survey will be conducted in the final year, in 2029.

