### Survey tool and variables

2.7

The survey is structured in five main sections (sociodemographic, health-related quality of life, critical health literacy, social connectedness, community capital, and knowledge, attitudes and practices on personal antibiotic use). The first section, which collects sociodemographic characteristics, will always be administered at the beginning of the survey. Participants will self-fill these questions on the interviewer's device, unless they request assistance, in which case the interviewer will read them out. This sociodemographic information will be used to analyse health inequalities within the study area, disaggregating the results by relevant social groups (by age, country of birth, race/ethnicity, sex, gender, etc.) and calculating both absolute and relative inequalities. The remaining four sections will be presented in a random order for each participant, using an algorithm embedded in the electronic form. This randomization of the remaining four sections (health-related quality of life, critical health literacy, social connectedness, community capital, and knowledge, attitudes and practices regarding personal antibiotic use) will allow the random and equitable distribution of potential biases in the understanding and answering of the questions, especially those at the end of the survey. The complete survey tool, variables, and response options can be found at the Supplementary Information of this protocol (Supplementary Supplementary Tables S2–S7).

The main outcome of the surveys is the health-related quality of life (HRQoL) measured using the VR-12 questionnaire. This tool has been internationally validated to measure HRQoL e (14). The VR-12 questionnaire contains 12 items that assess 8 aspects of health-related quality of life: physical functioning, physical role, bodily pain, general health, vitality, emotional role, social functioning and mental health. The VR-12 questionnaire measures these aspects in scales to produce a summary score in two dimensions: a physical dimension, represented by the Physical Component Summary, and a mental dimension, represented by the Mental Component Summary.

In addition, as secondary variables, a series of indicators will be measured with a descriptive and analytical purposes to also guide the co-creation process and a complementary role in the impact assessment as intermediate outcomes.

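### One common adjustment list turns the ethnicity, migration and education coefficients into residual associations that understate the social gaps the equity aim is about

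*Protocol article*

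**What the plan says.** Section 2.8 of the protocol article describes two kinds of group comparison.

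- **Descriptive.** The mean and standard deviation of HRQoL "will be calculated and stratified by sex, age group and other sociodemographic variables, thus allowing for an equity analysis". No age-standardisation is mentioned.
- **Model-based.** "we will perform multivariate models to analyse the association of sociodemographic characteristics on health-related quality of life and secondary variables". Further models are planned, "including interaction terms of time with sex, age group and other sociodemographic variables to assess the changes in social inequalities in HRQoL".

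One sentence then gives the covariates for the statistical analysis without limiting it to a particular model: it will be "adjusted for sex, age group and other sociodemographic variables such as education, ethnicity, migration status, household income, employment status and marital status", with others left open. No equity variable has its own adjustment set.

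The purpose is stated elsewhere. Section 2.7 (Survey tool and variables) says the sociodemographic data will be used for "disaggregating the results by relevant social groups (by age, country of birth, race/ethnicity, sex, gender, etc.) and calculating both absolute and relative inequalities". Section 2.1 (Study design) says: "Baseline results will inform the co-creation process by identifying community needs, health status and health inequities". The Introduction puts implications for health equity in the aim. Section 2.2 (Study setting) describes obstacles to schooling and work among Roma residents as harming their wellbeing, and links the area's vulnerability to migration and low income.

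**The concern.** The equity question is how large the gap is between, say, migrants and non-migrants of the same age and sex. If education, income and employment are among the ways in which being a migrant or belonging to a minority leads to worse HRQoL, a model that holds them fixed removes that part of the gap. Its coefficient answers a different question: how much difference remains between groups with the same schooling, income and work. The same applies to education once income and employment are held fixed.

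The article supplies the causal argument itself. Section 2.2 names education and employment as routes from Roma disadvantage to poorer wellbeing, and section 2.8 then adjusts for both. The Discussion expects migrants and racialised groups to report poorer health. The baseline results are meant to steer the co-created initiatives, so an understated gap could lower the priority given to the groups that the study wants to reach.

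**Working it through.** **The plan's own figures.** None bears on this point. The sample size in section 2.4 rests on the precision of one proportion and involves no adjusted model.

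**Structure.** For a linear model, write

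- total gap (age- and sex-adjusted) = D + M, where D is the part not running through income and employment and M is the part that does;
- M = sum over mediators of (effect of the mediator on the score) × (difference in its prevalence between groups);
- fully adjusted gap = D, so the share removed is M / (D + M);
- crude gap ≈ (D + M) + (age slope) × (difference in mean age).

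**Inputs.** Only the migrant share, 25.6% (section 2.3), comes from the document. The article gives no age, income or employment distribution by group and no effect sizes. Everything else is assumed: D = −1.5 points; low income in 55% against 30%; unemployment in 30% against 15%; each costing 3 points; score falling 0.2 points per year of age; residual SD 9.

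**By hand.** M = −3 × 0.25 − 3 × 0.15 = −0.75 − 0.45 = −1.2. Total = −1.5 − 1.2 = −2.7. Share removed = 1.2 / 2.7 = 44%.

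**Range.** Halve the two mediator effects: M = −0.6, share 0.6 / 2.1 = 29%. Double them: M = −2.4, share 2.4 / 3.9 = 62%. The share depends entirely on assumptions that the documents cannot settle.

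**Simulation under the first set of assumptions** (400,000 people per scenario, least squares; gaps in points):

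| Comparison | Crude | Age-adjusted | Fully adjusted |
|---|---|---|---|
| Migrants, same mean age | −2.67 | −2.70 | −1.51 |
| Migrants 5 years younger | −1.69 | −2.70 | −1.50 |
| Migrants 10 years younger | −0.77 | −2.74 | −1.54 |
| Migrants 15 years younger | +0.25 | −2.65 | −1.46 |
| Low education, commoner at older ages | −4.92 | −2.75 | −1.55 |

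Two things follow. Full adjustment shrinks the gap in every row, whatever the age structure. The crude gap moves with age, and its direction depends on the group: it is too small or reversed where the disadvantaged group is younger, and too large where it is older.

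**Time-by-group terms.** The change in the gap is (change in D) + (change in M). If the relation of group to income and employment is the same in both surveys, and so are their effects on the score, the change in M is zero and the reduced and full models estimate the same interaction. If, for example, the migrants' excess of low income vanished by the second survey, the gap would narrow by 3 × 0.25 = 0.75 points. The reduced model would show this narrowing; the full model would show none of it.

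**The case against.** The strongest reply has four parts.

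1. **The common list is an inference.** The covariate sentence follows the before-after models, uses open-ended wording, and does not say that all terms enter each inequality model. Exposure-specific sets are often left to an analysis plan, which is not shown. This stands in part. But the sentence is unrestricted, no other set is offered for the baseline models, and the interaction models come just before it. As written, the article fixes one list; the point is about that stated choice and not about missing detail.

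2. **Disaggregated means are what section 2.7 promises.** This stands. Crude means show the actual burden by group and are relevant to identifying needs. They are not an age-comparable gap, so they complement the model estimates and cannot replace them.

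3. **The authors speak only of association.** This also stands. Nothing in the article says that a residual coefficient will be read as the whole inequality. The difficulty is that no other adjusted estimate of the gap is described.

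4. **Section 2.8 already warns about p-values and type II error in small subgroups.** This does not answer the point. Adjusting for a pathway changes the quantity estimated, not only its precision.

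A reader might also infer that age hides the gaps in the crude tables for all groups. The documents give no age distribution by group, and for education the illustration goes the other way. A reader might infer that the time-by-group terms are necessarily biased. They differ between the two models only if the link from group to income or employment, or the effect of these on the score, changes between surveys.

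**Conclusion.** The point holds for the baseline inequality models. Followed as written, section 2.8 yields ethnicity, migration and education coefficients that leave out whatever runs through education, income and employment. They attenuate the social gap; they need not abolish it. This rests on two assumptions: that the shared list enters these models, which is its plain reading, and that the disadvantaged groups fare worse on education, income or work, with HRQoL suffering for it. Sections 2.2 and the Discussion point that way. The size cannot be computed from the documents; 29% to 62% in the illustration shows only how far it depends on what is assumed.

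The stratified means are valid as description but may be distorted by age in either direction. For change in inequality, the choice of covariates matters only under the condition given above. Adjusting the overall before-after contrast for case mix is a separate question, defensible with independent samples, and is not challenged here.

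**What to change.** Amend section 2.8 as follows.

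- For each equity variable, name as the main inequality estimate the absolute and relative gap from its own model, adjusted for age, sex and only those factors that precede it. For example: ethnicity or migration status with age and sex; education with age, sex and migration status.
- Show age-standardised means beside the crude stratified means.
- Keep the fully adjusted model as a secondary, explanatory analysis, labelled as the part of the gap not accounted for by the other variables.
- Report the time-by-group terms with the same reduced set alongside the fully adjusted one, and comment where they differ.

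The cost is a few lines of text, some extra regressions and more models to present. No new data are needed. The sample size and the case-mix adjustment of the overall before-after contrast stay as they are. The post-intervention survey is planned for 2029, so its analysis can still be specified this way, and the baseline equity report can use the same models.
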